### Statistical analysis

All statistical analysis will be carried out by the professionals using the SPSS (version 22.0) software. The statistical analysts will be unclear about the specific grouping content of the trial. In the present study, we will use a full analysis set (FAS) and per-protocol set (PPS), and the final conclusion will be based on the results of FAS. The full analysis set (FAS) is based on therapeutic intent. Patients who participate in the randomization but only have received 1-time treatment will also be included in the analysis. In the FAS analysis, for patients who do not complete the trial, the main indicators missed will be derived from the last observation carried forward (LOCF). All statistical analysis will be performed by bilateral differential test, with a *P* value < 0.05 considered statistically significant. Continuous variables will be presented as mean ± standard deviation (normally distributed data) or medians and ranges (non-normally distributed data). For the balance of basic values, analysis of variance or chi-square test or rank sum test will be used. For the primary and secondary outcomes, the analysis of variance will be used. If confounding factors may have an impact on the results, then the co-variance analysis will be used. Further, we will repeat measurements of the same outcome index of the same group at different time points. Changes involved in the rates before and after treatment in each group will be measured by the chi-square test or non-parametric test. The paired *t* test will be used to compare the differences between the groups before and after treatment.

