### Outcomes

In order to reduce the bias of experimental results, the following outcomes will be assessed by an independent outcome evaluator. Before the beginning of the trials, we will conduct a training session for the outcome evaluator. Further, we conducted online meetings via Tencent Meeting due to the ongoing COVID-19 pandemic.

The outcome evaluators will be performed at four time points including the baseline, on day 10 after the onset, on day 30 after the onset, and on day 45 after the onset (follow-up period).

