### Main outcome indicators

The primary evaluation index in the trial will be related to the change of the scores involved in the Sunnybrook (Toronto) Facial Grading System (SFGS) on the baseline and day 30 after the onset.

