### Sample size estimation

According to the previous studies [34], the difference between the SFGS score before and after treatment in the oral administration of prednisolone tablets group was 32.3, with a standard deviation of 8.1. The SFGS score before and after treatment for oral administration of prednisolone tablets combined with electroacupuncture intervention group reached up to 38.3, and the standard deviation was recorded 1. Obtained results were compared with the means of two independent samples. This study was a prospective study with two groups and the sample size was 1:1. The sample size was calculated using the formula $$ n=\frac{\left({Z}_{\alpha }+{Z}_{\beta}\right)2\times \left(1+1/k\right){\sigma}^2}{\delta^2} $$, with a test efficiency of 80%, a beta of 0.2, and an alpha of 0.025. The results show that the number of samples in each group was not less than 36. Considering the problem of missing samples or failing to follow-up, the sample size will be increased by 10%. This means that the minimum sample size of each group will be 40 patients. Finally, the total sample size of the two groups should not be less than 80 patients.

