## Discussion

Bell’s palsy, is the most frequently encountered type of peripheral facial palsy. It is an acute and self-limiting form of inferior motor neuron palsy. However, some part of patients cannot recover to the condition before the illness. The only prognostic factor of IFP is the state of the facial nerve 1 week after the onset [35], and the treatment in the acute phase of the disease largely determines the fate of FN and the recovery of facial function. Therefore, finding an effective treatment 1 week after the onset of illness is essential for an optimistic recovery. Previous studies have proved that steroids can relieve facial nerve edema. However, due to the compression state formed in the facial nerve canal in the acute phase, local blood circulation can be impaired. This may prevent oral steroids from reaching effective blood concentration in the facial nerve canal lesion, thereby affecting the efficacy and becoming a bottleneck in treatment. Stimulating the facial nerve canal through electroacupuncture locally may promote blood circulation in the facial nerve canal and relieve inflammatory edema. At the same time, improvement in the local microcirculation creates favorable conditions for the drug to reach effective blood concentration.

Worldwide, IFP is considered to be one of the most suitable indications for acupuncture treatment. Acupuncture has become the main treatment for IFP and exhibited significant effect according to the results of preliminary systematic evaluation and clinical studies. Electroacupuncture therapy is a kind of stimulation which directly acts on the target nerve through a combination of local acupuncture stimulation and electrical stimulation. Whether electroacupuncture can be used in the acute phase is still a subject of controversy. However, in the present study, the implementation of electracupuncture was scientific, detailed and innovative. Combining the theories of traditional acupuncture with modern anatomy, we select the Yifeng (SJ17) and Tinghui (GB2) electroacupuncture points to intervene in the acute phase of IFP; it will act directly around the target nerve.

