In the design of clinical trials, the selection of appropriate outcome indicators is critical to evaluate the clinical efficacy. Nowadays, most evaluation methods related to facial nerve function of patients mostly rely on neurological function scales and electrophysiological data and cannot easily observe changes in symptoms and condition. Hence, in the present study, we not only used a series of evaluation scales certified by international guidelines, but also used more intuitive detection technologies such as surface electromyography and MRI, which can evaluate the clinical efficacy before and after the treatment. Surface electromyography can more objectively reflect the recovery of the patient’s facial muscle function, whereas MRI can more directly reflect the recovery of facial nerve edema from the morphology. Moreover, we used NRS to evaluate the degree of pain behind or around the ear, although this symptom did not observe in all the patients. However, according to the epidemiological survey on IFP in the early years, the incidence of pain behind or around the ear is 63% [42], which often affects the recovery of the condition. Therefore, we conducted a statistical analysis and analyzed the degree and duration of pain.

However, this study also has few limitations. First, due to the particularity of acupuncture, we could not blind acupuncturists and patients; however, only evaluators and statisticians were blinded as much as possible. Second, the time interval between follow-up visits was too long, with no other follow-up points set due to the limited research funding and time. Part of the reason was related to the patient’s complex compliance problem. Most patients ended the cycle of follow-up observation in advance after meeting the remarkable improvement of acupuncture treatment. Nevertheless, this research will provide reliable evidence of efficacy and safety for the clinical treatment related to IFP.

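### Carrying the last SFGS score forward for patients lost before day 30 assumes that recovery stops in a recovering disease, and this rule sits in the analysis that decides the trial

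*Protocol article*

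**What the plan says.** The Statistical analysis section names a full analysis set and a per-protocol set and states that "the final conclusion will be based on the results of FAS". Within the FAS, "for patients who do not complete the trial, the main indicators missed will be derived from the last observation carried forward (LOCF"). Entry to the FAS needs little exposure: "Patients who participate in the randomization but only have received 1-time treatment will also be included in the analysis".

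The Main outcome indicators section defines the primary outcome as the "change of the scores involved in the Sunnybrook (Toronto) Facial Grading System (SFGS) on the baseline and day 30 after the onset". The Outcomes section lists the assessments as follows: "four time points including the baseline, on day 10 after the onset, on day 30 after the onset, and on day 45 after the onset". Table 1 shows SFGS at the same times. Only two SFGS scores therefore precede the primary time point: baseline and day 10.

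On the course of the disease, the Discussion says: "It is an acute and self-limiting form of inferior motor neuron palsy". The Sample size estimation section plans on mean SFGS gains of 32.3 (prednisolone) and 38.3 (combination). It also allows for loss: "Considering the problem of missing samples or failing to follow-up, the sample size will be increased by 10" per cent.

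**The concern.** LOCF is harmless only if a patient's score would have stayed where it was last seen. Here the protocol's premises point the other way. The disease recovers by itself, the planned control gain is more than 30 points, and both arms receive nine electroacupuncture sessions between day 11 and day 30, so further gain after day 10 is expected by design.

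For a patient lost before day 30, the imputed day-30 score is the day-10 score or, if that too is missing, the baseline score. In the second case the change is exactly 0, in a distribution centred on 32 to 38. Three things follow:

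- the difference between arms is pulled toward zero when loss is equal;
- the variance rises, because the imputed values sit far below the rest;
- if loss differs between arms, the arm that loses more looks worse, whatever the treatment does.

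The rule applies in the analysis that decides the trial.

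**Working it through.** **Inputs from the protocol.** Control gain 32.3, SD 8.1; experimental gain 38.3, so the difference is 6.0; 36 per group, raised to 40; 10% loss; two-sided test at 0.05 in the analysis.

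**Assumptions.**
- SD is 8.1 in both arms. The protocol prints 1 for the experimental arm; see the last step.
- f is the share of a patient's day-30 gain already present in the carried score. f = 0 means baseline is carried. The protocol gives no day-10 mean, so a range is shown.
- Loss is unrelated to outcome. Any split of loss between arms is assumed.

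**The plan's own figure.** n = (z₀.₉₈₇₅ + z₀.₈)² × 2 × 8.1² / 6² = (2.241 + 0.842)² × 3.645 = 34.6, or 35; the t-based version gives 36. So 36 is reproduced with SD 8.1 and alpha 0.025 two-sided. 36 / 0.9 = 40. At the two-sided 0.05 level of the analysis, power is 0.91 with 40 per arm and no loss, and about 0.88 with 10% lost at random and not imputed. The fair comparator for LOCF is 0.88.

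**Mean and variance under LOCF.** With a fraction p lost in an arm whose full gain has mean m and SD s:
- mean = m × [1 − p(1 − f)]
- variance = (1 − p)s² + p f² s² + p(1 − p)(1 − f)² m²

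Example, control arm, p = 0.10, f = 0: variance = 0.9 × 65.61 + 0.09 × 32.3² = 59.05 + 93.90 = 152.9, so the SD is 12.4 instead of 8.1. For the experimental arm it is 59.05 + 0.09 × 38.3² = 191.1, SD 13.8.

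**Equal loss, 10% in each arm, true difference 6.** The estimate is 6 × [1 − 0.1(1 − f)]. Power is from simulation (two-sample t test, 20,000 runs).

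| f | Estimate | Power |
|---|---|---|
| 0 | 5.40 | 0.45 |
| 0.25 | 5.55 | 0.60 |
| 0.5 | 5.70 | 0.76 |
| 0.75 | 5.85 | 0.87 |
| not imputed | 6.0 | 0.88 |

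Hand check at f = 0: SE = √[(152.9 + 191.1)/40] = 2.93 and 5.4/2.93 = 1.84, just below the critical value, which agrees with power of about 0.45. Most of the power loss comes from the variance and little from the smaller difference. With no true difference, type I error stays near 5%.

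**Unequal loss, 15% control and 5% experimental, no true difference.** Bias = (0.15 − 0.05) × (1 − f) × 32.3.

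| f | Bias (points) | Type I error |
|---|---|---|
| 0 | 3.2 | about 20% |
| 0.5 | 1.6 | about 12% |
| 0.75 | 0.8 | about 7% |

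Nearly all of these false positives favour electroacupuncture.

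**Reverse split, 5% control and 15% experimental, true difference 6.** Estimate = 38.3 × [1 − 0.15(1 − f)] − 32.3 × [1 − 0.05(1 − f)].
- f = 0: 32.56 − 30.69 = 1.9
- f = 0.5: 35.43 − 31.49 = 3.9
- f = 0.75: 36.86 − 31.90 = 5.0

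Power is 0.11 at f = 0 and 0.45 at f = 0.5.

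**With the printed experimental SD of 1.** The pattern is the same: at 10% loss in each arm, power is 0.53 (f = 0) to 0.98 (f = 0.75), against 0.99 without imputation.

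**The case against.** The strongest reply is that the damage depends on when patients leave and from which arm, and the protocol fixes neither. Much of this stands.

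- **Who is affected.** A reader might infer that every dropout is frozen at day 0 or day 10. That is not so. The trial runs to day 45, and anyone lost between days 31 and 45 already has the primary score.
- **Outcome-related loss.** The Discussion says: "Most patients ended the cycle of follow-up observation in advance after meeting the remarkable improvement of acupuncture treatment". A reader might take this as proof that missing day-30 scores depend on outcome. The sentence comes in a limitation about follow-up visits, Table 1 uses the follow-up label for days 31 to 45, and nothing places the stopping before day 30. If such patients did leave before day 30, their last score would already hold much of the gain, so f would be high and the harm smaller. The figures above do not use this remark.
- **Unequal loss.** The 15% and 5% split has no source in the protocol. Controls receive the same electroacupuncture from day 11, treatment is free and all participants get reminders. On the other hand, treatment is open to patients and the acute-phase visit burden differs, so unequal loss cannot be ruled out in either direction.
- **Loss of power is not universal.** If controls are lost more often and the effect is real, the rejection rate stays at about 0.88 to 0.94 for f from 0 to 0.5, but only because the estimate is inflated to between 7.5 and 8.9.
- **Day 45.** A reader might infer that the rule discards a day-45 score when only day 30 is missed. LOCF is stated for patients who do not complete the trial, and someone seen at day 45 may count as a completer. The text does not settle this.
- **Per-protocol analysis.** One is planned, but the conclusion does not rest on it.

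None of this makes a halt in recovery a reasonable assumption for the deciding analysis.

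**Conclusion.** The point holds for patients lost before day 30. For them the primary score is replaced by one that assumes no further recovery, against the protocol's own account of the disease and its planned gains.

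At the planned 10% loss, equal in both arms, the cost is a slightly diluted difference and power somewhere between 0.45 and 0.87 for f from 0 to 0.75, against about 0.88 without imputation, with no inflation of type I error. If loss is unequal, the same rule can produce a false positive or hide a real effect, and the direction cannot be known in advance. If most of the recovery is reached before loss (f of 0.75 or more), the harm is small.

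These sizes rest on SD 8.1 in both arms, loss unrelated to outcome, assumed values of f and, for the biased scenarios, an assumed split. The low end, power of 0.45 or type I error of 20%, needs every lost patient to leave with only a baseline score. It is a bound and should not be read as a forecast. The protocol does not support a claim that loss before day 30 is outcome-related or unequal, only that the chosen rule gives poor protection if it is.

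**What to change.** Make the primary FAS analysis a likelihood-based repeated-measures model of SFGS at the scheduled visits, with visit and arm-by-visit terms and the day-30 contrast between arms as the primary estimate. The FAS admits patients who may have only a baseline score. To keep them in the model, enter baseline as one of the responses, with a common mean across arms, and not as a covariate. Keep LOCF as a sensitivity analysis. Ask for the scheduled day-30 SFGS from patients who stop treatment early and are willing to be assessed.

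The analysis change is a matter of wording, uses visits already scheduled and should be settled before the allocation is revealed to the analysts. Seeking day-30 scores after treatment stops is a small change in conduct and takes slight follow-up effort; with recruitment due to end in April 2021, it can help only patients not yet past that visit. The statistical price is reliance on missing at random, which is a weaker assumption here than that recovery stops at the last visit.

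A summary of loss by arm and by last SFGS visit would show the reader which part of the range above applies.

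### The primary SFGS change gets an unadjusted analysis of variance by default, with baseline adjustment left to an undefined confounding condition; a fixed ANCOVA on baseline SFGS is better and costs nothing

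*Protocol article*

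**What the plan says.** All references are to the protocol article.

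- Main outcome indicators defines the primary outcome as "the change of the scores involved in the Sunnybrook (Toronto) Facial Grading System (SFGS) on the baseline and day 30 after the onset".
- Statistical analysis gives the default model: "For the primary and secondary outcomes, the analysis of variance will be used". The next sentence gives the exception: "If confounding factors may have an impact on the results, then the co-variance analysis will be used". No covariate, criterion or time of decision is attached to it.
- The sentence before the default plans tests of baseline comparability: "For the balance of basic values, analysis of variance or chi-square test or rank sum test will be used".
- The same paragraph ends with another between-group procedure: "The paired *t* test will be used to compare the differences between the groups before and after treatment".
- Baseline SFGS is available. Outcomes lists "four time points including the baseline, on day 10 after the onset, on day 30 after the onset, and on day 45 after the onset", and Table 1 schedules SFGS at enrolment.
- Sample size estimation compares two independent mean changes with no baseline term. The control change "in the oral administration of prednisolone tablets group was 32.3, with a standard deviation of 8.1"; the experimental change is 38.3, with the SD printed as 1.

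**The concern.** Randomisation removes systematic confounding, so whether confounding may be at work is not a useful question for choosing the primary model. Baseline SFGS should be in the model because it is likely to predict the outcome and because the arms may differ at entry by chance. Both reasons are known in advance and call for adjustment in every case.

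Baseline severity probably matters here. The entry criteria set no severity range, the randomisation section describes no stratification, and the Background calls the disease self-limiting with usually good recovery. How far a patient can improve therefore depends partly on the starting score.

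Two things are at stake. One is precision given up without need. The other is a primary result that rests on a judgement with no stated rule, because two analyses of the same outcome both fit the text.

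**Working it through.** **Inputs.** From Sample size estimation: mean changes 32.3 and 38.3, so a difference of 6.0; SD 8.1; alpha 0.025; power 80%; 36 per group, raised to 40. From Statistical analysis: two-sided 0.05. The documents do not give the baseline to day-30 correlation (rho) or the two variances. These are assumptions, and a range is shown.

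**1. Reproduce the plan's figure.** With SD 8.1 in both arms and two-sided alpha 0.025:

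n = 2 × [8.1 × (2.241 + 0.842) / 6.0]² = 34.65, so 35 per group. The t-test version gives 35.9, so 36, as stated. Adding 10% gives 36 × 1.10 = 39.6, so 40.

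Two other readings do not give 36: SD 8.1 with two-sided 0.05 gives 29, and pooling SDs of 8.1 and 1 gives 15 to 18. The calculations below therefore use 8.1 in both arms. The calculation behind the plan's figure is an unadjusted comparison.

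**2. Relative variance.** Let r be the day-30 SD divided by the baseline SD. Then

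var(ANCOVA) / var(change) = r²(1 − rho²) / (1 + r² − 2·rho·r).

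For r = 1 this is (1 + rho)/2, which is 0.65, 0.75 and 0.85 for rho 0.3, 0.5 and 0.7.

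**3. Power at 36 per group.** Unadjusted: 6.0 / (8.1 × √(2/36)) = 3.143, and Φ(3.143 − 1.960) = 88.2%. For ANCOVA, divide 3.143 by the square root of the ratio. For example, with rho 0.5, 3.143/√0.75 = 3.629 and Φ(3.629 − 1.960) = 95.2%.

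| Analysis (r = 1) | Two-sided 0.05 | Two-sided 0.025 |
|---|---|---|
| Unadjusted change | 88.2% | 81.6% |
| ANCOVA, rho 0.3 | 97.4% | 95.1% |
| ANCOVA, rho 0.5 | 95.2% | 91.7% |
| ANCOVA, rho 0.7 | 92.6% | 87.9% |

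Over the wider range of rho from 0.2 to 0.9, ANCOVA power at two-sided 0.05 runs from 98.2% down to 89.7%.

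**4. Unequal variances.** With r = 2 and rho = 0.5 the ratio is 4 × 0.75 / (1 + 4 − 2) = 1.0, so nothing is gained. This happens when the slope of day 30 on baseline (rho × r) is near 1. With r = 0.5 and rho = 0.5 the ratio is 0.25, a larger gain. Apart from one lost degree of freedom, ANCOVA does not do worse.

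**5. Chance imbalance.** At 40 per arm the standard error of the baseline difference is √(2/40) = 0.22 SD. With rho 0.5 and r = 1, the SD of change equals the baseline SD (8.1). An imbalance of one standard error is then 0.224 × 8.1 = 1.8 points. It moves the unadjusted difference by (1 − 0.5) × 1.8 = 0.9 points, which is 15% of the 6-point target. ANCOVA removes that shift.

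**6. Type I error** (40,000 simulated null trials, 40 per group, r = 1, nominal 5%).

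- Unadjusted change alone: 4.8 to 5.0%. Fixed ANCOVA alone: 4.7 to 5.1%.
- The smaller of the two p values: 7.8%, 7.0% and 6.7% for rho 0.3, 0.5 and 0.7.
- ANCOVA only after a significant baseline test: 4.1 to 4.7%.

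**The case against.** The strongest reply is that this is a condensed article and that covariates and adjustment criteria are commonly left to an analysis plan, which is not shown. That stands for the missing covariate list. It does not cover the conditional sentence, which the article itself states: a plan that follows it inherits the switch, and one that does not contradicts it.

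Several stronger readings are tempting, and the documents do not support them.

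- **The baseline tests trigger the switch.** A reader might infer this from the order of the sentences, but the text never links them. Even if they were linked, that rule did not inflate type I error in the simulation.
- **The change score is biased.** Over all randomisations it is unbiased. The shift in step 5 is an error given the observed imbalance, and the standard error already allows for such imbalance.
- **The trial is underpowered without adjustment.** On its own inputs it has about 88% power at two-sided 0.05.
- **The power gain is a known amount.** It depends on rho and on the variance ratio, and neither is given.

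Analyst blinding, promised under Blind method, Statistical analysis and Quality control, is also a fair defence against choosing the smaller p value. It lowers that risk. It does not remove it, because two p values can be compared with the arms coded.

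Finally, the paragraph also mentions repeated measurements, so the analysis of variance might be a repeated-measures one, and it names a paired t test for a comparison of groups. These are separate uncertainties, but they add to the impression that the primary test is not uniquely fixed.

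**Conclusion.** The point holds as an improvement that should be made. It is not a flaw that invalidates the trial. The protocol makes an unadjusted analysis the default and lets adjustment depend on a condition that is undefined and, in a randomised trial, the wrong one.

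Under equal variances and SD 8.1 in both arms, always adjusting for baseline SFGS raises power at 36 per group and two-sided 0.05 from about 88% to about 97%, 95% or 93% for rho 0.3, 0.5 or 0.7. With unequal variances the gain can shrink to about zero, at the price of one degree of freedom. The 7 to 8% type I error is a worst case that requires picking the smaller p value; nothing in the documents says that this is intended. Because the trial is adequately powered on its own inputs, the open choice of model is the stronger argument and the power gain the weaker one.

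**What to change.** Before unblinding, replace the default and the conditional sentence with one primary model: ANCOVA of day-30 SFGS (or its change) on arm, with baseline SFGS always included, reporting the adjusted mean difference and 95% CI. Keep the unadjusted analysis of variance as a sensitivity analysis, and state that no result of a baseline comparison alters the primary model.

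Use the same form for the continuous secondary scores that have a baseline (NRS and FDI). House-Brackmann is an ordinal grade and needs an ordinal method instead of linear ANCOVA.

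The cost is about one sentence for the primary outcome and one for the secondary outcomes. No new data, visits or patients are needed, because baseline SFGS is already scheduled.

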**Methods:**

Randomized controlled trials will be conducted in the first teaching hospital of Tianjin University of Traditional Chinese Medicine in China from September 2020 to April 2021. The treatment will be carried out in two phases, including the acute phase and the recovery phase. Eighty IFP patients will be recruited and randomized into two groups with a 1:1 ratio. Subjects in the acute phases of the control group will be given oral prednisone tablets, based on the control group, and subjects of the experimental group will be given electroacupuncture therapy simultaneously in the acute phase. Both groups will be stopped taking prednisone tablets and turn to electroacupuncture therapy in a recovery phase. Patients in the experimental group will receive treatment at least 6 times in the acute phase and both groups will receive treatment 9 times in the recovery phase, and there will be a follow-up period of 15 days after the treatment. The primary outcome is supposed to be related to the changes observed in the Sunnybrook (Toronto) Facial Grading System (SFGS) on the baseline and day 30 after the onset. Secondary outcome measures will include House-Brackmann Facial Nerve Grading System (H-B), measurement of Numerical Rating Scale (NRS), Facial Disability Index scale (FDI, including physical function subscore, FDIP, and social functioning and well-being subscore, FDIS), surface electromyogram (sEMG), and magnetic resonance imaging (MRI). Adverse events will be recorded for safety assessment.

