## Method/design

### Study design

The proposed study is a parallel-group superiority randomized controlled trial with a 1:1 allocation ratio and a blind method for evaluation. We will compare the effects of two available treatment options for patients with IFP in the acute phase. The study will include the treatment phase and follow-up period. Trial procedures are described in Fig. 1, whereas Table 1 illustrates the trial schedule. In total, 80 IFP patients will be recruited and randomized into one of two groups with a 1:1 ratio of the experimental group (oral prednisone tablets combined with electroacupuncture) and the control group (simple oral prednisone tablets). In the present study, patients will be recruited from the First Affiliated Hospital of Tianjin University of TCM from September 2020 to March 2021. All patients will be required to provide written consent to participate in the study. This study is approved by the Ethics Committee of the First Affiliated Hospital of Tianjin University of TCM (TYLL2020[K]049). Furthermore, to carry out this study, we registered the study in the Chinese Clinical Trial Registry (ChiCTR2000038472).

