#### House-Brackmann facial nerve grading system

The House-Brackmann Facial Nerve Grading System was introduced by John W. House and Derald E. Brackmann. It can evaluate the patient’s facial nerve function status and classify the patient’s facial nerve damage integrally. The grading system is easy to understand and applied quickly to clinical practice relatively [32]. The measurements will be performed within the baseline, day 10 after onset, and day 30 after onset. The number of cases reaching grade 1 on the 30th day after the onset of illness also will be counted.

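### The analysis section names a paired t test for a comparison between two independent arms, in competition with the valid ANOVA already assigned to the same contrast

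*Protocol article*

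**What the plan says.** All places are in the protocol article.

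- **Study design:** "The proposed study is a parallel-group superiority randomized controlled trial with a 1:1 allocation ratio and a blind method for evaluation".
- **Sample size estimation:** the comparison is described as "Obtained results were compared with the means of two independent samples".
- **Main outcome indicators:** the primary outcome is the change in SFGS from baseline to day 30.
- **Statistical analysis, outcomes:** "For the primary and secondary outcomes, the analysis of variance will be used". Covariance analysis is added only if confounding is thought to matter. No exception is made for graded or binary outcomes.
- **Statistical analysis, rates:** "Changes involved in the rates before and after treatment in each group will be measured by the chi-square test or non-parametric test".
- **Statistical analysis, last sentence:** "The paired *t* test will be used to compare the differences between the groups before and after treatment".
- **Statistical analysis, baseline:** "For the balance of basic values, analysis of variance or chi-square test or rank sum test will be used". This is the only place where a rank sum test is named.
- **House-Brackmann section:** besides the grade at baseline, day 10 and day 30, "The number of cases reaching grade 1 on the 30th day after the onset of illness also will be counted".

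**The concern.** A paired t test needs a natural link between the members of each pair. Patients randomised to different arms have no such link. The sentence that assigns this test to the groups therefore contradicts the design and the basis of the sample size.

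The sentence is not peripheral. A between-group difference in before/after change is exactly what the primary outcome measures, and ANOVA has already been assigned to it. An analyst who follows the section finds two tests for one contrast and no rule on which takes precedence. If the sentence is instead read as a within-arm test, its result says nothing about electroacupuncture, because the protocol itself calls the disease self-limiting (Rationale for the use of intervention; Discussion).

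Two smaller mismatches stand beside it. Before/after rates within an arm come from the same patients, yet an ordinary chi-square test is one of the options. ANOVA is also prescribed for every secondary outcome, which includes a graded scale that has a binary count beside it.

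**Working it through.** **1. What the sample size assumes.** Inputs from Sample size estimation: changes of 32.3 and 38.3, so δ = 6.0; SD 8.1; power 80%; alpha 0.025. The two-independent-sample formula with alpha taken as two-sided gives

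n = (2.2414 + 0.8416)² × 2 × 8.1² / 6.0² = 9.505 × 131.22 / 36 = 34.6, so 35 per group.

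The exact t version gives 35.93, so 36, which is the plan's figure. The 10% allowance then gives 40. The stated size thus rests on an independent-samples comparison with SD 8.1.

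**2. The paired t test taken literally, across arms.** An arbitrary pairing would have to be imposed.

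| Test, 36 per arm, δ = 6.0, SD 8.1 | Power, two-sided 0.025 | Power, two-sided 0.05 |
|---|---|---|
| Independent t (same as two-arm ANOVA) | 80.1% | 87.3% |
| Paired t on arbitrary pairs | 78.5% | 86.3% |

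Simulated type I error for the arbitrary pairing is 5.0% at a nominal 5%. With 40 per arm the degrees of freedom are 39 instead of 78, which moves the two-sided 5% critical value from 1.99 to 2.02. The numerical cost is therefore small. The real defects are that the result depends on which patients are matched, and that the test cannot use all patients when the arms differ in size.

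**3. The paired t test read as a within-arm test.** Control arm, n = 40:

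- standard error = 8.1/√40 = 1.281
- t = 32.3/1.281 ≈ 25.2

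In simulation with a change of 32.3 and SD 8.1, every run rejected at 5%. The control arm has no acute-phase electroacupuncture, so this result needs no effect of the treatment under test.

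**4. Chi-square on before/after rates in the same patients.** With equal true rates p at both times and within-patient correlation ρ, the variance of the difference in proportions is 2p(1−p)(1−ρ)/n. Pearson chi-square uses 2p(1−p)/n. Its approximate type I error at nominal 5% is therefore P(|Z| > 1.96/√(1−ρ)). The documents give no ρ, so a range is assumed; the simulations use n = 40 and an assumed rate of 0.40.

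| ρ (assumed) | Pearson, formula | Pearson, simulated | McNemar, simulated |
|---|---|---|---|
| 0 | 5.0% | 5.3% | 5.3% |
| 0.3 | 1.9% | 2.1% | 4.6% |
| 0.5 | 0.6% | 0.6% | 4.3% |
| 0.7 | 0.03% | 0.03% | 4.6% |

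Under positive correlation, ignoring the pairing makes the test conservative.

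**5. ANOVA for House-Brackmann.** No arithmetic applies. The scale is described as a grading system with a grade 1, so it is ordered. ANOVA treats the steps between grades as equal. The number at grade 1 on day 30 is a binary outcome, for which ANOVA is not a fitting method. The only test named for rates compares before with after within an arm, which does not compare the arms.

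**The case against.** The strongest reply is that the last sentence is a misworded within-group test. It follows statements on repeated measurement in the same group and on before/after change in each group, and nothing in the section rests the efficacy conclusion on it. That reading is plausible, but the sentence still names the groups as the things compared and needs correcting.

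The reply also rules out several stronger inferences.

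- A reader might infer that the trial has no valid primary analysis. It has one: ANOVA on SFGS change in two arms is the independent t test and agrees with the sample size.
- A reader might infer that within-arm significance will be reported as efficacy. The documents state no such rule. The t of about 25 shows only that a within-arm test would be uninformative.
- A reader might infer that chi-square on paired rates produces false positives. With positive within-patient correlation the error runs the other way. The alternative of a non-parametric test could also cover McNemar, so the point is that an unsuitable option remains open.
- A reader might infer that ANOVA on House-Brackmann grades is invalid. It is suboptimal, and the outcome is secondary.

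It can also be said that a between-arm test for the grade-1 count may be left to an analysis plan that is not shown. That is fair as to detail. What can be faulted is the blanket assignment of ANOVA to all secondary outcomes.

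**Conclusion.** The point holds as an error of wording and test assignment that should be corrected before analysis. The paired t sentence contradicts the parallel-group design and competes with a valid test for the primary contrast. Followed literally, it costs about 1.6 percentage points of power (80.1% to 78.5% at 36 per arm, two-sided 0.025) and leaves a result that depends on an arbitrary pairing. Followed within arms, it does not address superiority.

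The sample size and the ANOVA comparison are unaffected, so this is not a fatal flaw. The chi-square and House-Brackmann points are secondary.

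The figures rest on the plan's change scores and its control SD of 8.1 applied to both arms, on alpha 0.025 read as two-sided where power is quoted at that level, and on assumed within-patient correlations and a rate of 0.40 for the chi-square check.

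**What to change.** - Delete the paired t test as a between-group test.
- Name one between-arm primary analysis: ANCOVA of SFGS adjusted for baseline SFGS, in place of ANOVA with covariance analysis only on condition.
- Compare House-Brackmann grade between arms by a rank-sum test or an ordinal model.
- Compare grade 1 at day 30 between arms by a risk difference with 95% confidence interval, with a chi-square or Fisher test.
- Keep paired t, Wilcoxon signed-rank and McNemar as within-arm summaries, labelled descriptive.

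The cost is a few sentences in the analysis section. The data are already scheduled for collection, and neither the number of patients nor the visits change.
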